### Sample size determination

Findings from the pilot study were combined with literature on the clinically meaningful difference in SF-36 total scores for patients with TBI between groups (0.3 standard deviations) to perform the power analysis for this study.[32, 87] For this study, a total of N = 356 individuals will provide 80% power for the study design described above (α = 0.05, two-tailed) to detect a small effect size between study arms (Cohen’s d = 0.18). A sample size of N = 356 represents 178 patient/family dyads with 89 dyads randomly assigned to the treatment arm and 89 dyads randomly assigned to the usual transitional care management arm. Based on our preliminary studies, we anticipate that 10% of eligible participants will decline participation and that 10% of recruited/enrolled participants will be lost to follow-up.[32] As such, to account for attrition, our enrollment goal is N = 436 individuals (218 patient/family dyads; 109 dyads per arm). It worth noting that the power calculations were performed only for the primary outcome, patient QOL changes in SF-36 total scores from baseline to 16 weeks post-hospital discharge, to test our central hypothesis. We powered this study to detect a small effect size to ensure we can detect the minimal clinically important difference.^31^

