### Measures

Detailed list of data collection measures and timeframes of data collection are outlined in Table 1. Our team has secured the existing Spanish versions of data collection measures. Data collection measures not available in Spanish have been culturally and linguistically translated from English to Spanish (forward and back translation), and we obtained and incorporated feedback from native Spanish speakers into our translations. Details on our translation process are published elsewhere [44].

**Table 1 pone.0296083.t001:** Data to be collected & time points for treatment & usual transitional care management arm dyads of adults with TBI and families (Aim 1).

		Administered to		Data collection times			
				Pre-	Post-discharge		
Measures / Type of Data to Be Collected	Description / Construct of focus	Patient	Family	Pre-	8 wks	16 wks	24 wks
Demographics	Age, sex, race/ethnicity, education, pre-injury occupation, insurance status, annual income	X	X	X			
Patient clinical factors (via chart review)	TBI severity, length of stay, comorbidities	X		X			
^+^Short Form-36 (SF-36)—primary outcome	Quality of life (QOL); SF-36 is commonly used to assess QOL in patients with TBI	X		X	X	X	X
NeuroQOL, Cognitive functioning	Cognitive functioning status	X		X	X	X	X
NeuroQOL, Upper & Lower extremity functioning (separate measures)	Physical functioning status	X		X	X	X	X
NeuroQOL, Sleep Disturbance	Sleep disturbances	X		X	X	X	X
Rivermead Post-concussion Questionnaire (RPQ)	TBI-related symptoms	X		X	X	X	X
PART-O	Participation	X			X	X	X
Care Transitions Measure-3 (CTM-3)	Process of care transitions	X			X	X	X
Service Obstacles Scale (SOS)	Difficulty in accessing services	X	X		X	X	X
EuroQol (EQ-5D-5L) + VAS (visual analogue scale) + Cognitive domain (C)	Health status, including five dimensions (i.e., mobility, self-care, usual activities, pain/discomfort, anxiety/depression) and the VAS, with the cognitive domain (C) added for patients only	X	X	X	X	X	X
Interpersonal Processes of Care (IPC)	Multi-dimensional interpersonal processes in the clinical encounter	X	X	X	X	X	X
*Patient Health Questionnaire-9 (PHQ-9)	Depressive symptoms	X	X	X	X	X	X
Self-Efficacy for Management of Chronic Conditions Scale	Confidence in chronic TBI management	X	X	X	X	X	X
CAGE-AID Substance Abuse Screening Tool	Alcohol and substance use	X	X	X	X	X	X
Self-Reported Health Literacy Questions	Personal health literacy	X	X	X			

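### The stated inputs do not support 80% power for d = 0.18: with 89 patients per arm, power is 22% unadjusted, and 51% at the plan's own 0.3 SD

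*Protocol article*

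**What the plan says.** All the power figures stand in the protocol article under Sample size determination. It says that "a total of N = 356 individuals will provide 80% power for the study design described above". The test is two-sided at the 0.05 level, and the stated aim is "to detect a small effect size between study arms (Cohen’s d = 0.18". The headcount is then converted as follows: "A sample size of N = 356 represents 178 patient/family dyads with 89 dyads randomly assigned to the treatment arm", with the same number in usual care. It limits the calculation to the primary outcome, "patient QOL changes in SF-36 total scores from baseline to 16 weeks post-hospital discharge". It also cites a "clinically meaningful difference in SF-36 total scores for patients with TBI between groups (0.3 standard deviations", and closes by saying that the study was powered for a small effect so that the minimal clinically important difference can be detected.

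Table 1 (Measures) lists "Short Form-36 (SF-36)—primary outcome" with a single mark for who completes it. Instruments given to both dyad members carry two. The Primary outcome measure section describes the SF-36 as patient-reported. Data analysis names repeated measures ANOVA as the primary method and 16 weeks as the primary endpoint. Data collection expects 16-week data from 80% of dyads.

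**The concern.** The power statement is made for 356 individuals, but half of them are family members who supply no SF-36. The primary analysis has 178 outcomes. The section also carries two effect sizes, d = 0.18 and 0.3 SD, and does not say how they relate.

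At stake is the assurance that the trial can detect its own clinically meaningful difference. If real power at 0.3 SD is near one half, a true benefit of that size could easily be missed, and readers of the protocol would have been told otherwise.

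**Working it through.** **Inputs from the article.** Two-sided alpha 0.05; 1:1 allocation; 89 dyads per arm, so n = 89 patients per arm; d = 0.18; clinically meaningful difference 0.3 SD; primary endpoint at 16 weeks.

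**Assumed, because not stated.** The baseline-to-16-week correlation r, shown from 0.3 to 0.7 (0.8 for the repeated-measures check).

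**1. Trying to reproduce the stated 80%.** Two-sample t-test, noncentrality = d × √(n/2), df = 2n − 2.

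| Outcomes per arm | d | Noncentrality | Power |
|---|---|---|---|
| 89 (patients) | 0.18 | 0.18 × √44.5 = 1.20 | 22% |
| 178 (all 356 people counted) | 0.18 | 0.18 × √89 = 1.70 | 40% |
| 89 (patients) | 0.30 | 0.30 × √44.5 = 2.00 | 51% |
| 178 (all 356 people counted) | 0.30 | 0.30 × √89 = 2.83 | 80.6% |

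For 80% power at d = 0.18 the test needs 486 patients per arm; at 0.30 it needs 176. All 109 enrolled patients per arm would give 26% at d = 0.18. The 22% applies directly if d is in SDs of the change score, the outcome that the section names, or in SDs of the 16-week score without adjustment.

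**2. Baseline adjustment.** If d is in SDs of the raw score, adjustment gives an effective d of d / √(1 − r²).

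| r | Power at 0.18 | Power at 0.30 |
|---|---|---|
| none | 22% | 51% |
| 0.3 | 24% | 55% |
| 0.5 | 28% | 63% |
| 0.7 | 39% | 80% |

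Reaching 80% at d = 0.18 with 89 per arm needs r of about 0.905.

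**3. The repeated-measures route.** For two equal groups compared once, f = d/2 = 0.09. Entered in a standard arm-by-time routine with N = 178 patients, m = 4 visits and r = 0.5, the noncentrality is f²Nm/(1 − r) = 0.0081 × 178 × 4 / 0.5 = 11.5, and power is 82%. It is 80% at r of about 0.47 with four visits and 0.55 with three.

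In that test, however, f is half the root mean square deviation of the arm differences around their average over visits. Setting f = 0.09 and solving for the largest arm difference x:

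- (0, x), two visits: f = x/4, so x = 0.36 SD
- (0, x, x, x): f = 0.2165x, so x = 0.42 SD
- (0, x/2, x, x): x = 0.43 SD
- (0, x/3, 2x/3, x): f = 0.1863x, so x = 0.48 SD

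Conversely, a sustained difference of 0.18 SD over three follow-ups has f = 0.039. The same test with 178 patients then has 16%, 20%, 32% and 47% power at r = 0.3, 0.5, 0.7 and 0.8. Averaging the three follow-ups with baseline adjustment gives 44% to 71% over the same range, but that is not the 16-week endpoint.

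**4. Smallest difference with 80% power.** At 89 per arm: 0.42 SD unadjusted, 0.37 SD at r = 0.5, 0.30 SD at r of about 0.7. An 80% collection rate gives 0.80 × 218 = 174 dyads, about 87 per arm, and 0.43 SD unadjusted.

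**The case against.** The strongest reply is that the power is claimed for the described design, which is repeated measures ANOVA over several visits, and not for a t-test at one visit. The correlation and software settings may properly sit in the full protocol or the SAP. A repeated-measures calculation with f = 0.09 uses the stated d and the correct unit, patients, and reaches 80% at ordinary correlations. On that view 356 is only the headcount of 178 dyads.

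Part of this stands. Leaving the correlation out of an article is not an error, and the 22% must be labelled as the unadjusted or change-score case. But the repeated-measures route does not rescue the sentence as written. The article claims "to detect a small effect size between study arms" of 0.18 with 16 weeks as the endpoint, and the arm-by-time f of 0.09 describes a difference at least twice that size.

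Two stronger readings are tempting and go too far. A reader might infer that the 80% is impossible; a correlation of about 0.905 would deliver it, and the article does not state the value used. A reader might also infer that family members were counted as outcomes, because 356 fits 0.3 SD at 80.6%. That is one possible origin only: the same count gives just 40% at d = 0.18, and the repeated-measures route arrives at 178 patients without it.

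It is also fair to say that what a null result excludes is decided by its confidence interval and not by planned power.

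**Conclusion.** The concern holds as a mismatch between the stated power and the stated inputs. For the between-arm SF-36 difference at 16 weeks, 89 patients per arm have 22% power at d = 0.18 unadjusted and 24% to 39% with baseline adjustment at assumed correlations of 0.3 to 0.7. At the plan's own 0.3 SD, power is 51% unadjusted and 55% to 80% adjusted. The claim of power for the minimal clinically important difference therefore rests on a correlation of about 0.7 or more, which the article neither states nor justifies.

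These figures assume complete data on 89 patients per arm, equal variances and the correlations shown. The baseline-adjusted comparison stands in for the 16-week contrast from the planned model. The cause of the discrepancy remains open.

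**What to change.** Rewrite the power paragraph under Sample size determination:

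- Give power in patients per arm, since only patients supply the SF-36, and keep the dyad headcount for recruitment.
- State power for the 16-week between-arm difference from the planned repeated-measures model, with the effect-size metric, number of visits and assumed correlation. For example: 89 evaluable patients per arm give 80% power for 0.42 SD unadjusted, 0.37 SD at a correlation of 0.5 and 0.30 SD at about 0.7. Also give the figure for about 87 per arm (0.43 SD unadjusted), which the 80% collection rate implies.
- Remove or correct d = 0.18 and explain how it relates to 0.3 SD.
- Drop the statement that the study is powered for the minimal clinically important difference, unless a correlation of about 0.7 or more is justified, for instance from the pilot data.

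The cost is one paragraph and a less favourable power statement. The planned analysis does not change and no patients are added.

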### Timeline

The timeline of this RCT is described in Table 2. Before starting, we obtained IRB approval. Aims will occur simultaneously and take 4 years and 9 months (6 months to hire and train interventionist; 3.25 years to recruit, enroll, and collect data; 1 year for analysis and dissemination). The timeline of this study was informed by our feasibility study.

**Table 2 pone.0296083.t002:** Timeline of the randomized controlled trial.

	Pre	Year 1				Year 2				Year 3				Year 4				Year 5		
Study Activities	Pre	Q1	Q2	Q3	Q4	Q1	Q2	Q3	Q4	Q1	Q2	Q3	Q4	Q1	Q2	Q3	Q4	Q1	Q2	Q3
Obtain IRB approval																				
Hire/train interventionists & research coordinators																				
Recruitment / enrollment																				
Data collection																				
Interventionist supervision																				
Data analyses (all aims)																				
Disseminate (publications & presentations)																				
Annual reporting																				

## Discussion

The objective of this RCT is to examine the efficacy of BETTER[30–32] (vs. usual transitional care management) among diverse adults with TBI and families. The proposed study aims to drive advancements in health equity through the inclusion of English- and Spanish-speaking participants, Black and Latino patients with TBI and family caregivers (who historically have poorer outcomes vs. Whites), and populations with limited or no access to care. This study also aims to improve systems and models of care by testing the efficacy of a new, TBI transitional care model.

Existing TBI-specific transitional care interventions have not been culturally or linguistically designed or adapted to address the needs/preferences of Spanish-speaking patients and families or allow for the inclusion of Spanish-speaking patients and families. To address this gap in research and practice, it is important for research and clinical teams to build the capacity to address the needs of Spanish-speaking patients with TBI and their families.[88] Access to Spanish-speaking professionals during the transitional care process, interpreters, and educational materials and content in Spanish is one important step in addressing transitional care needs of Spanish-speaking patients with TBI and their families.[89]

Findings from the trial will provide new knowledge to inform transitional care research for diverse adults with TBI and families and will generate evidence to improve public health and drive equitable advancements in care by reducing systemic and structural inequities in place for minoritized communities, with the goal of improving health equity.[90] This study’s findings will formally establish the efficacy of BETTER, informing future implementation and dissemination trials. Study findings may ultimately shift the standard of care for adults with TBI discharged home from acute hospital care and families and can inform the development of U.S. TBI transitional care standards.
